### Methods in analysis to handle protocol non-adherence and any statistical methods to handle missing data {20c}

No imputation of missing data will be performed for statistical analysis.

### Plans to give access to the full protocol, participant-level data and statistical code {31c}

The full trial protocol will be shared on reasonable request. Anonymised data on the group level may be shared with outside investigators at the end of the trial after receiving institutional approval for releasing the data externally. The findings of this trial will be published in peer-reviewed journals and presented at conferences. The results of the study will be released to the participating patients.

## Oversight and monitoring

### Composition of the coordinating centre and trial steering committee {5d}

The trial will be conducted by the study research team, including the Goulburn Valley Health Obstetrics and Gynaecology Department and Goulburn Valley Health Research and Ethics Unit, in collaboration with the Obstetrics and Gynaecology Department staff. The principal investigator takes responsibility for supervision of the trial and ensures compliance with the study protocol. Vaginal cleansing prior to CS will be performed by the obstetrics and gynaecology study team clinicians. A third person with adequate clinical acumen independent to the project will assess the post-CS infection to reduce any potential bias, for example, the obstetrics and gynaecology consultant on call and obstetrics and gynaecology registrar. The statistical research plan and statistical analysis will be supervised by the Research and Ethics Unit, Goulburn Valley Health.

### Composition of the data monitoring committee, its role and reporting structure {21a}

The data monitoring committee is unnecessary in this trial, because this study will not involve participants with severe diseases and communication disabilities or interventions that can risk participants’ lives. Instead, the oversight of data quality will be provided by the Research and Ethics Unit, Goulburn Valley Health.

### Adverse event reporting and harms {22}

Since the proposed interventions in this study are safe and commonly used for vaginal cleansing prior to CS, no severe adverse events relating to the interventions are expected after careful enrolment following the specified exclusion criteria. However, all study patients will be monitored with respect to any possible adverse events related to the administration of interventions. As such, all adverse events (AEs) observed or reported by the patient are collected and evaluated for relatedness to trial intervention, seriousness, severity, expectedness and outcome. AEs are defined in the Good Clinical Practice (GCP) guideline.

### Frequency and plans for auditing trial conduct {23}

For the quality assurance, 5% randomly selected questionnaire from the collected information will be re-interviewed. Any discrepancies will be corrected accordingly. In addition, the study team will audit the data regularly. An audit may be performed by Goulburn Valley Health Research and Ethics Unit, its designee or regulatory agencies to evaluate the clinical study conduct and compliance with the protocol, standard operating procedures, GCP and the applicable regulatory requirements.

### Plans for communicating important protocol amendments to relevant parties (e.g. trial participants, ethical committees) {25}

The principal investigator will be responsible for any protocol amendments and their subsequent processes. Protocol amendments will be submitted to the Ethics Committee and implemented only after approval is received. It will be the responsibility of the principal investigator to disseminate the changes to the protocol, and all study research team members will be adequately trained on protocol amendments.

### Dissemination plans {31a}

The study findings will be presented internally in the Goulburn Valley Health Hospital for service improvement, externally in national or international conferences. A full scientific article will be developed and published in peer-reviewed journal/s. The results of the study will be released to the participating patients.

## Discussion

Post-operative infectious morbidity still complicates CS deliveries despite the widespread use of prophylactic antibiotics [3]. Although there is evidence suggesting that vaginal cleansing with antiseptic wash before CS reduces infection rates, different antiseptics have been practised inconsistently and there is no standard of practice for the uniform use of antiseptic agents, or a particular antiseptic agent, for vaginal toileting to reduce post-CS infections or complication. In this blinded randomised controlled clinical trial, we will evaluate the use of antiseptic wash for vaginal cleansing prior to CS and aim to determine the best antiseptic wash and methods to reduce post-CS infection. We hypothesise that the interventions, chlorhexidine or povidone iodine, will improve the rate of infection including post-operative infective complications within 28 days of CS by 50% compared to no vaginal irrigation. To test our hypothesis and meet the study aims and objectives, we will recruit 375 pregnant women giving birth by CS (*n* = 125 per group) over a 16-month period. The primary and secondary outcomes will be measured over 28 days post-CS to enable the determination of study conclusions. Given that rates of CS delivery are increasing worldwide [2], it is important to ensure that risks to the mother are as minimal as possible; therefore, the results of this study may provide important data to define the future uniform use of vaginal antiseptic wash immediately prior to CS and to determine the best antiseptic wash material in reducing post-operative infections or complications. This study is strengthened by (1) its focus on the investigation of infection rates in complex patient profiles comprising many comorbidities and high BMI rates and (2) the capacity to add data from a regional population since regional data is lacking in the current body of literature. Possible limitations include the study only being conducted at one regional hospital and that the rate of post-CS infection is already low.

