#### Aims

The aims are to introduce uniform use of vaginal antiseptic wash immediately prior to CS and to determine the best antiseptic wash material in reducing post-operative infections or complications.

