### Sample size {14}

We assume that the interventions will improve the rate of infection including post-operative infective complications (within 28 days post-CS) by 50% compared to the control. Thus, for sample size estimation in this study, we set *P*_1_ = 8% (as per overall prevalence of post-CS infection range 3–15%), *P*_2_ = 4%, significance level = 5% and the study power = 80%.

Therefore,
$$ n\ge {\left(\frac{Z_{\alpha }+{Z}_{\beta }}{\mathrm{ES}}\right)}^2 $$$$ \mathrm{ES}=\frac{P_1-{P}_2}{\sqrt{P_1\left(1-{P}_1\right)}} $$

*n* ≥ 361

Here, *Z*_*α*_ = 1.96, *Z*_*β*_ = 0.84, *P*_1_ = 0.08, *P*_2_ = 0.04 and *P*_1_ − *P*_2_ = 0.04.

Considering 10% dropout, the study will require recruiting approximately 396 participants for all the groups (*n* = 132 in each group) over a period of 16 months to adequately test the assumption.

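### The stated sample size is tied to finding the best antiseptic, but the sizing covers only antiseptic against control, and arms of this size say little about chlorhexidine against povidone iodine

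*Protocol article*

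**What the plan says.** The Aims section of the protocol article sets two goals. The second is "to determine the best antiseptic wash material in reducing post-operative infections or complications". The fourth item under Objectives turns this into a product: a uniform guideline resting on locally generated evidence about which wash is best. The Discussion repeats the goal and attaches a number to it: "To test our hypothesis and meet the study aims and objectives, we will recruit 375 pregnant women giving birth by CS", with 125 per group.

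Sample size {14} is the only place where a size is derived. It starts from one effect: "We assume that the interventions will improve the rate of infection including post-operative infective complications (within 28 days post-CS) by 50% compared to the control". Control is set at 8%, and a single rate of 4% stands for the interventions together. The result, 361, is raised for 10% dropout to about 396, or 132 per group. The hypothesis is likewise about either antiseptic against no irrigation.

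Statistical methods {20a} plans ANOVA across the groups and, where appropriate, logistic regression of the interventions against control. It does not name a chlorhexidine against povidone iodine contrast.

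**The concern.** Naming the best antiseptic requires comparing the two antiseptics with each other. The sizing does not address that comparison: it specifies no difference between them, so no power can be read from it. Yet the Discussion presents the recruited number as serving the aims and objectives, this one among them.

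The intended product is a guideline. With very few events in each antiseptic arm, a small numerical lead could be taken as the answer to the stated aim, or a non-significant difference could be taken to show that the two washes are equivalent. Arms of this size would ordinarily support neither conclusion.

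**Working it through.** **Inputs**
- Control rate P1 = 8%, intervention rate P2 = 4%, Z values 1.96 and 0.84, 10% dropout, 132 per group: Sample size {14}.
- 125 per group: Discussion (375/3).
- 119 per group: derived here as 132 × 0.9 = 118.8, that is, 132 less the planned dropout.
- The second antiseptic's rate: not given in the document, so every value other than 4% and 8% is an assumption.

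**1. The plan's own figure.** ES = (0.08 − 0.04)/√(0.08 × 0.92) = 0.1474, and n = ((1.96 + 0.84)/0.1474)² = 360.6, rounded up to 361. The figure reproduces. Adding 10% gives 361 × 1.1 = 397, close to the stated 396, and 396/3 = 132. Only P1 and P2 enter. With one P2 for both antiseptics, the planned difference between them is zero.

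**2. Precision with both antiseptics at 4%.** Expected events per antiseptic arm are 119 × 0.04 = 4.8, 125 × 0.04 = 5.0 and 132 × 0.04 = 5.3. The 95% half-width for the difference is 1.96 × √(2 × 0.04 × 0.96/n):
- n = 119: 5.0 points
- n = 125: 4.9 points
- n = 132: 4.7 points

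Each exceeds the whole 4-point effect planned against control.

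**3. Power with one antiseptic at 4%.** Two-sided 5%, normal approximation, with p̄ the mean of the two rates:

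power = Φ[(|pA − pB|√n − 1.96√(2p̄(1 − p̄))) / √(pA(1 − pA) + pB(1 − pB))]

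Example, 4% against 2% at n = 125: (0.02 × 11.180 − 1.96 × 0.2412)/0.2408 = −1.03, so power is 15.0%.

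| Other antiseptic (assumed) | n = 119 | n = 125 | n = 132 |
|---|---|---|---|
| 1% | 31.6% | 32.9% | 34.4% |
| 2% | 14.5% | 15.0% | 15.6% |
| 3% | 6.2% | 6.3% | 6.4% |
| 6% | 10.5% | 10.8% | 11.2% |
| 8% | 25.4% | 26.4% | 27.6% |
| Rate giving 80% power | 14.5% | 14.1% | 13.8% |

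The rate needed for 80% power lies well above the 8% assumed for control. In the other direction, even 4% against 0% reaches only about 64% at 132 per arm. Fisher's exact test is lower still: for 4% against 2%, 6.6% at 125 and 7.2% at 132.

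**4. Size that the contrast would need.** For 80% power before dropout: 1,141 per arm for 4% against 2%, and 5,301 per arm for 4% against 3%.

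**5. Antiseptic against control.** The same formula for 8% against 4% gives 25.4%, 26.4% and 27.6% power per pair at 119, 125 and 132. Pooling both antiseptics against control gives 37%, 38% and 40%. The standard two-proportion calculation needs about 553 per arm. The formula in the plan has a one-sample form, and its result is used as the total for three arms.

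**The case against.** The strongest reply has four parts.

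- *Secondary aims of multi-arm trials are often not powered.* True, and lack of power alone would not be a fault. But the Discussion links this number of women to the aims and objectives, and the sizing gives no basis for that link.
- *The Discussion sentence states a purpose, not power.* This is fair. A reader might infer a claim that every aim is adequately powered, but the sentence does not say so. The Discussion also says only that the results may provide important data, and it lists the low infection rate as a possible limitation. Sample size {14} claims only to test the assumed reduction against control. What remains is the link between the size and an aim that the size was not built for.
- *Correcting the sizing would settle this too.* It would not. About 553 per arm for 8% against 4% is still far short of the 1,141 per arm for 4% against 2%.
- *A separate analysis plan may add the contrast.* It may, but that would not change the precision available.

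Four stronger readings are tempting and go beyond the text. First, a reader might infer that the two antiseptics cannot be separated at all. That depends on holding one at 4%: with assumed rates of 8% and 0.5%, power is 82% at 119 per arm and 86% at 132. Second, a reader might infer that the plan asserts equal efficacy, but it only uses one planning rate against control. Third, with both truly at 4%, one arm has a lower observed rate by chance in about 87% of trials at 119 per arm. That is not an error rate of this trial, because the protocol has no rule for choosing by raw point estimate. Fourth, because the sizing concerns antiseptic against control, a reader might infer that this contrast is secure. Step 5 of the working shows that it is not.

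**Conclusion.** The point holds in this form: the stated size does not support the best-antiseptic aim to which the Discussion attaches it. If one antiseptic has the planned 4% rate, the interval for the difference is about ±5 points, halving that rate would be detected about 15% of the time, and 80% power needs a second rate of about 14%. The conclusion is the same whether the trial recruits 375 or 396, both of which appear in the article.

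The figures refer to the broad infection outcome used in Sample size {14}. The primary outcome is endometritis alone, for which no rate is given. At an assumed 2% in each arm, the half-width would be about 3.5 points (1.96 × √(2 × 0.02 × 0.98/125)).

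This is a fault in what the trial says it can conclude. It does not mean that the arms should not be compared, and it does not certify the antiseptic against control contrast, whose sizing needs its own correction.

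**What to change.** - **Discussion:** remove the statement that this number of women meets the best-antiseptic aim. Say that the sizing considered only antiseptic against control, without implying that this contrast is adequately powered. Correct the calculation in Sample size {14} as a separate matter.
- **Aims and fourth objective:** reword as estimating the chlorhexidine minus povidone iodine risk difference with its 95% confidence interval, as a secondary exploratory comparison. Name the outcome and give the expected precision for it (about ±5 points at a 4% rate).
- **Interpretation:** state that no antiseptic will be named best, and no equivalence claimed, unless that interval supports it.

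The cost is wording in three places and one additional contrast on data already collected. It needs no extra patients. The downside is a more modest stated aim.

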## Trial status

Protocol version number: 6

Protocol date: 18 December 2020

Recruitment start date: September 2020

Planned recruitment end date: December 2021

## Abbreviations

AE: Adverse event
CS: Caesarean section
ERA: Enhanced recovery after caesarean delivery
GCP: Good Clinical Practice
m/cs: Microscopic examination, culture and sensitivity
PICF: Participant information and consent form
SSI: Surgical site infection
WHO: World Health Organization
